## Background

Fear of childbirth (FoC) is a highly prevalent negative emotion among pregnant women characterized by high levels of stress and emotional maladaptation to the normal physiological and psychological processes of being pregnant and giving birth [1, 2]. Reports demonstrate that approximately 25 % of pregnant women suffer from a high level of FoC, as assessed by the Wijma Delivery Expectancy/Experience Questionnaire (W-DEQ-A and B), defined as a W-DEQ-A score ≥66 [3]. Besides, approximately 10 % of pregnant women have been found to suffer from severe FoC (W-DEQ-A score ≥85) [4]. The complex causes of FoC can be examined from a biopsychosocial perspective [5] that includes biologically-oriented dimensions of fear (e.g., fear of pain, fear of bodily harm, or fear of one’s own or one’s infant’s death), psychological factors (e.g., personality traits, a history of traumatic life events or previous difficult or traumatic obstetrical experiences, feelings of helplessness, or anxiety about motherhood), and social factors (e.g., dissatisfaction with the partner relationship, lack of social support, low socioeconomic status, hearing ‘horror stories’ about labour from family, friends, acquaintances, and media sources) [1, 6, 7]. FoC can be categorized as ‘primary FoC’ occurring in nulliparous women (first-time mothers) and ‘secondary FoC’ following a previous difficult or traumatic childbirth experience. Differences in severity of FoC between nulliparous and parous women are still being investigated [8, 9]. FoC seems to be a specific domain of anxiety associated with, yet distinct from, general anxiety or depression [10]. Only a small number of studies have evaluated the content and interrelationship of pregnant women’s FoC and their partners’ FoC [11, 12]; the role of fathers’ perinatal distress as a contributing factor to FoC among pregnant women is still unknown.

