## Methods

### Design

The study design is a quasi-experimental controlled trial with two arms (intervention and active comparison group) involving four assessment time points. Participants will be allocated by the order of inclusion in the study (alternation). Inclusion will take place at baseline 16–26 weeks gestational age. Subsequently, questionnaires will be filled in one-two weeks pre-intervention (T1) and post-intervention (T2), and two-four weeks (T3) and 16–20 weeks (T4) following the birth. Participating couples will receive a fee of €50 upon completion of data collection (T4).

Participants from an urban area in The Netherlands will be quasi-randomized to the intervention (MBCP) or comparison group (FoCC) using an Excel program of created codes with the intent of producing equivalent training group cohorts of approximately six participants each. The flowchart of the study design and participants is depicted in Fig. 2.

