### Sample size

Assuming a medium effect size of MBCP compared to the comparison condition and referrals of 30 % from primary to secondary midwifery care due to maladaptation to childbirth [28] we aim to include *n* =128 pregnant women with a high level of FoC and their partners (64 couples in each arm) to achieve a power of 80 % to find a significant effect (test of between-within interaction, 5 % alpha, 0.5 correlation). We based our power calculations on a medium effect size versus the large effect size found in a single-group trial of MBCP for decreasing pregnancy anxiety (*d* = 0.81, *p* < 0.0001) in the study of Duncan and [name] [40] and the overall medium mean effect size of MBP’s (*d* = 0.59) [55], in part due to the unknown effect size of the FoCC comparison condition.

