### Statistical analyses

#### Primary analyses

Dichotomous outcome data will be analysed using Chi-square tests or logistic regression using the method of ‘last observation carried forward’ (i.e., assuming no change) to handle dichotomous incomplete data. Continuous outcome data will be analysed with Multi-level analyses. Multi-level analyses with full information maximum likelihood (FIML) estimation use all available data and allow intention-to-treat analyses including all participants with incomplete data and participants who dropped out during the study. Continuous variables will be transformed into *Z*-scores. In this way, the parameter estimates can be interpreted as a measure of effect: i.e., as Cohen’s *d* for dichotomous predictors and as *r* for continuous predictors. Outliers will be identified. Analyses will be run twice: once in which all original scores will be included and once in which outliers will be changed to *Z*-scores (-) 3.29. Dependent variables will be level of FoC, labour pain and willingness to accept obstetrical interventions without medical indications. Predictors will be the different time measurements (T2, T3, and T4 against T1) and condition (MBCP versus FoCC). Interaction effects of time X condition will be added to the model to examine which programme is more effective over time.

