Some limitations to this study design need to be considered. First, the quasi-experimental study design creates less homogeneous groups then with full randomization (RCT) and permits a greater risk of bias due to potential alternation and allocation problems. To work with this, we adopted the recommendations for designing the Q-RCT studies from the Cochrane Handbook for Systematic Reviews of Interventions [86]. Due to the steadily increasing gestational age, dependency on recruitment speed and efficiency, and the required size of approximately six participants in the intervention group, we are obliged to use the quasi-randomization procedure in order to be able to conduct this study efficiently. A second limitation is the uncertainty of the power of this study due to the unknown effect size of the comparison group. To cover this limitation, we have chosen to downsize the expected large effect size of MBCP as shown in Duncan and [name]’s [40] study to a medium effect size in order to not under-power our study. An additional limitation is the potentially sizable dropout of participants due to their possibly strong preferences for one of the study’s interventions, the nine weeks duration of the programmes, and the relatively long and direct follow up after the birth. As a retention strategy we provide the participants with a financial incentive (€50) for completing the measurements following the birth.

Among the strengths of this study are the clinical-based experimental design, the extensive cognitive-emotional and behavioural measurements in pregnant women and their partners during the entire perinatal period, and the representativeness of the study sample as well as the generalizability of the study’s results. The complex and innovative measurements of FoC in this study are an important strength in research on FoC not only in pregnant women but also in their partners.

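### Allocation is by alternation, yet the stated primary model carries no baseline covariate, so imbalance in factors that predict change, above all across the birth, passes into the effect

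*Protocol article*

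**What the plan says.** - **Allocation** (Design): "Participants will be allocated by the order of inclusion in the study (alternation". No stratification by parity, gestational age or city is described. The section on quasi-experimental allocation gives rising gestational age, recruitment speed and the minimum MBCP group size as the reasons for the scheme.
- **Admitted weakness** (Discussion): "the quasi-experimental study design creates less homogeneous groups then with full randomization (RCT) and permits a greater risk of bias". The remedy cited there is a set of recommendations for designing such studies. No analytic adjustment is named.
- **Primary model** (Primary analyses): "Predictors will be the different time measurements (T2, T3, and T4 against T1) and condition (MBCP versus FoCC". The next sentence reads: "Interaction effects of time X condition will be added to the model to examine which programme is more effective over time". The dependent variables are fear of childbirth, labour pain and willingness to accept obstetrical interventions.
- **Dichotomous outcomes** (Primary analyses): chi-square tests or logistic regression, with no covariate named.
- **Population** (Participants, Inclusion criteria): first-time and multiparous women, 16 to 26 weeks pregnant, from two cities.
- **Parity** (Background): "Differences in severity of FoC between nulliparous and parous women are still being investigated". The same paragraph separates primary fear, in first-time mothers, from secondary fear after a difficult or traumatic birth.

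**The concern.** When allocation is not random, the analysis is the last place to protect the comparison from baseline differences. Here the article states the predictor list for the primary outcomes, and that list offers no protection beyond the T1 score.

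Whether the T1 score is enough depends on the outcome. It works where the same quantity is measured before and after. It works less well across the birth. Table 4 shows fear measured by W-DEQ-A at T1 and T2 but by W-DEQ-B at T3 and T4, and the pain VAS moves from expected to experienced pain. A woman who has given birth before may well differ in how her expectation relates to her experience, so parity is a plausible predictor of that change. NPSI-SF, SIL, BSES-SF, BISQ and the birth outcomes from the medical report have no T1 value, so nothing cancels for them.

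At stake is an imbalance being read as a programme effect, or hiding one. If the covariates are not named in advance, any later adjustment is open to the charge of post hoc selection.

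**Working it through.** **1. The plan's own figure.** The Sample size section states the effect as: "Assuming a medium effect size of MBCP compared to the comparison condition", with 64 per arm "to achieve a power of 80 % to find a significant effect (test of between-within interaction, 5 % alpha, 0.5 correlation". Medium is taken as d = 0.5 and alpha as two-sided; both are assumptions, since neither is printed. With correlation 0.5, the SD of change is sqrt(2 x (1 - 0.5)) = 1. The normal approximation gives 63 per arm. The t-test gives 63.8, so 64 per arm with power 0.801. The planned size is therefore reproduced as a test of difference in change with no covariates.

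**2. What omission does to that test.** Bias in the time x condition effect = imbalance x effect of the factor on change. For a 20-point parity imbalance:

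| Effect of parity | Bias | Share of d = 0.5 |
|---|---|---|
| Level only | 0 | 0% |
| 0.3 SD on change (assumed) | 0.20 x 0.3 = 0.06 | 12% |
| 0.5 SD on change (assumed) | 0.20 x 0.5 = 0.10 | 20% |

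Simulation with 64 per arm and a true effect of -0.50 agrees. The unadjusted estimate averaged -0.50, -0.44 and -0.40 in the three cases. With a covariate x time term it averaged about -0.50 in all three. The standard error was about 0.18 with or without the term.

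**3. How large an imbalance is plausible.** For a factor present in half the women (assumed), a purely random split has SD sqrt(2 x 0.25/64) = 0.088, so 95% limits of about ±17 points. A gap of 10 points or more has probability 0.26. Twenty points is thus a little beyond ordinary chance and serves as a stress case for alternation. A 10-point gap halves the bias to 0.03 to 0.05.

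**4. Which form of adjustment works.** In a two-wave mixed-model data set the time x condition estimate was:

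| Model | Estimate | SE |
|---|---|---|
| No covariate | -0.575 | 0.187 |
| Covariate main effect | -0.575 | 0.187 |
| Covariate x time | -0.684 | 0.184 |

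The same holds with four waves, a 19-point imbalance and parity altering change after birth by 0.5 SD. Without a covariate the estimate was -0.402 (SE 0.179), and a main effect left it identical. With about 20% dropout a main effect moved it by at most 0.03. Only covariate x time terms correct the primary test.

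**5. Precision.** With covariates explaining a share R2 of the variance of change, power = Φ(0.5/sqrt((1 - R2) x 2/64) - 1.96). This gives 0.807 at R2 = 0, then 0.815, 0.827 and 0.846 at assumed R2 of 2%, 5% and 10%. That is a gain of about 1 to 4 points.

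**The case against.** The strongest reply is that the tested effect is already a change contrast. T1 is the reference, the interaction carries the comparison, and the sample size is built on it. Level differences between the arms therefore cancel. This stands, and it limits the point to factors that predict change and to outcomes without a T1 value.

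Two stronger readings are tempting, and the documents do not support them:
- **A shift of 0.10 to 0.17 SD (20 to 35% of d = 0.5).** A reader might get this from 1.96 x sqrt(2/64) x an assumed correlation of 0.3 to 0.5. It describes a comparison of post-treatment means, not the planned interaction, and it treats chance imbalance, which the standard error already reflects, as bias.
- **A power gain from 80% to 84-92%.** This comes from a two-sample t-test with an assumed R2 of 10 to 30%. It does not describe the change test.

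It can also be said that the outcomes without a T1 value are secondary and that the quoted predictor sentence covers the primary dependent variables. This is right: the article does not fix the predictors of the secondary outcomes, and a separate analysis plan may do so. The article also says that referring clinicians cannot predict the group, and it already allows logistic regression. Finally, it gives no parity effect. The Background leaves differences in severity by parity open, so every effect size above is an assumption.

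What remains is a stated primary model with no baseline adjustment, in a trial whose authors concede a greater risk of bias, for measures whose content changes at birth.

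**Conclusion.** The point holds in limited form. The primary model as stated removes imbalance in level but not imbalance in predictors of change. The exposure is greatest for W-DEQ and pain VAS after birth, where the T1 measure is not the same quantity as the later one. The size is about 0.06 to 0.10 d for a 20-point parity imbalance, assuming parity shifts change by 0.3 to 0.5 SD, and zero if it shifts level only. The direction depends on which arm has more first-time mothers.

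Outcomes with no T1 value, and the dichotomous birth outcomes, have no baseline protection under an unadjusted analysis. For these the request is to settle the covariates in advance; the article makes no wrong statement about them.

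The case rests on protection from bias. The precision gain is secondary and small.

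**What to change.** Pre-name four covariates: parity (first birth or not), city, gestational age at T1 and screening W-DEQ-A score.

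- **Multilevel models with T1 as reference:** enter each covariate with covariate x time terms. Main effects alone do not alter the tested interaction.
- **Outcomes with no T1 value:** enter the covariates as main effects.
- **Dichotomous birth outcomes:** use logistic regression rather than the chi-square test, so that the covariates can enter.
- **Reporting:** give the unadjusted model alongside.

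The cost is analysis wording and some extra parameters: up to about 16 in the four-wave models (4 covariates x 4 waves), with almost no effect on the standard error in the checks above. Gestational age and W-DEQ-A are already obtained for eligibility, and city follows from the site. The article does not list parity as a collected item, but it describes the sample by parity, so its availability is assumed. Allocation, visits and sample size stay as they are.

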### Intervention: The Mindfulness-Based Childbirth and Parenting (MBCP) programme

The MBCP programme [40] developed in the United States by midwife and mindfulness teacher [name], CNM, MA, is a formal adaptation of MBSR specifically developed for the expectant parent population. The teachings of mindfulness through formal and informal meditations are fully integrated with the knowledge of the psychobiological processes in pregnancy, birth, breastfeeding, postpartum adjustment and the psychobiological needs of the infant. MBCP as developed by [name] includes nine weekly three-hour classes, a 7-hour day of silent meditation practice and a 3.5-hour reunion gathering after all the babies have been born. For purposes of this study, the standard MBCP was adapted (with permission by [name]). Two first classes were combined as Class 1 and the 7-hour day of silent meditation practice was reduced to one 3-hour class (see Table 2). Expectant parents are asked to commit to practicing the formal meditations at home for 30 min a day, six days a week with instructional CDs that are given as part of the course materials. Adherence to the intervention is assessed by reporting the number of classes attended and weekly diaries of the amount of time spent between sessions in formal daily meditation practice and being mindful of the activities of daily living (informal practices). The importance of keeping a meditation diary will be emphasized. Each MBCP course will be taught by an experienced midwife, who, in accordance with the MBCP protocol, has been trained as an MBCP teacher by [name]. All MBCP sessions will be video recorded to assure fidelity to the MBCP model. Ratings of fidelity to the MBCP model will be carried out by two independent raters. The MBCP sessions will be free of charge and take place at a Mindfulness Centre in Amsterdam and The Hague.

**Table 2 Tab2:** Outline of the Dutch Adaptation of the Mindfulness-Based Childbirth and Parenting Programme

Week 1	Background of mindfulness, the MBCP programme, introduction to mindfulness meditation through an eating meditation, awareness of breathing meditation.
Week 2	Body scan meditation, attitudinal foundations of mindfulness, community building.
Week 3	Awareness of breathing meditation, body scan meditation, psycho-education: physiology of childbirth from a body-mind perspective.

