### Active Comparison Condition: Fear of Childbirth Consultation (FoCC)

The target sample of pregnant women included in this study suffer from intense FoC. In order to acknowledge the fears of these women we have upgraded care as usual into structured consultations on FoC (FoCC). FoCC consists of an adaptation of the Biopsychosocial Model [5] and the Childbirth Plan of the Royal Dutch Organization of Midwives (KNOV) [59].

This individualized programme for expectant couples includes two consultation sessions with a trained midwife of one-hour each over a nine-week period (see Table 3). The aim of FoCC is to gain insight into the variety of specific factors playing a role in the origin and presence of fear and stress around pregnancy, birth and the postpartum period as well as designing a suitable coping plan based on the particular fears and stresses, and includes some components of psychoeducation about fear. A structured form is used to collect information about FoC related factors and for the coping plan. The coping plan may include referral to a psychologist or other mental health care services. All FoCC sessions will be audio recorded in order to assure treatment fidelity. Two recordings per consultation will be randomly selected and evaluated by an independent midwife. The free of charge FoCC sessions will take place at the participant’s midwifery practice or place of residence.

**Table 3 Tab3:** Outline of the Two Sessions of the Fear of Childbirth Consultations

FoCC First Consultation
Mapping of the bodily, mental and social factors underlying FoC and the postpartum period. Interview about the pregnant woman’s overall state of physical health and current pregnancy, her mental health and emotional state, her ideas and values regarding being pregnant, the process of giving birth and being a parent, incidence of psychopathology in her family of origin, her most severe fears about childbirth and the postpartum period, her relationship with her partner, family, presence of social support, workplace experiences, important life events and potential vulnerabilities. A written psychoeducation about FoC and matching behavior from a body and mind perspective is provided.
FoCC Second Consultation

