### Quasi-experimental allocation to the two study conditions

The allocation to the two study groups will be done on the sequence of entry into the study using an Excel program of created codes. This procedure ensures that the referral midwives and obstetricians are not able to predict the group to which the participant will be assigned. The choice for quasi-experimental allocation is based on a steadily increasing gestational age, dependence on recruitment speed and efficiency, and the required minimum group size of six participants in the MBCP intervention group.

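### The sample size makes no allowance for MBCP being taught in groups of about six while FoCC is individual, and the analysis text does not name training group as a level

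*Protocol article*

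**What the plan says.** **Delivery.** The Design section describes allocation "with the intent of producing equivalent training group cohorts of approximately six participants each". The section on quasi-experimental allocation gives as one of its reasons "the required minimum group size of six participants in the MBCP intervention group". The intervention section adds that "Each MBCP course will be taught by an experienced midwife", and Table 2 sets out nine weeks of shared classes. The comparison is different in kind: "This individualized programme for expectant couples includes two consultation sessions with a trained midwife".

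**Sample size.** The inputs are a medium effect, 80% power, 5% alpha, a correlation of 0.5 and a "test of between-within interaction". They lead to 128 women, 64 per arm. A 30% rate of referral to secondary care is also mentioned. No ICC, design effect or number of groups appears.

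**Primary analyses.** Continuous outcomes go into multi-level models with full-information maximum likelihood. The benefit given for this is that incomplete data can be used. The levels and random effects are not named. The predictors are the time points and condition ("T4 against T1) and condition (MBCP versus FoCC"), to which their interaction is added. Dichotomous outcomes are to be tested by chi-square or logistic regression.

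**The concern.** This is a partially nested design: one arm is clustered by course and the other is not. Women in the same MBCP course share a teacher, the classes and each other's company, so their changes in fear of childbirth may be correlated. The mean of the MBCP arm then varies more than 64 independent women would imply.

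Two things are at stake. The planned power is lower than stated, because the planning formula has no term for this. In addition, if the analysis also omits the group, its standard errors are too small, its intervals too narrow, and the nominal 5% test rejects too often.

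**Working it through.** **Inputs.** From the article: 64 women per arm, groups of about six, alpha 5%, correlation 0.5, and FoCC individual (cluster size 1). Assumed: d = 0.5 for a medium effect (no number is given), a two-sided test, and the ICC (none is given). The ICC meant here is that of the change from T1, because the tested term is time by condition. 64/6 = 10.7, so about 11 groups.

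**Step 1: reproduce 128.** With correlation 0.5, the SD of a change score is sqrt(2 × (1 − 0.5)) = 1 in baseline SD units. A pre-post interaction test is therefore a two-sample comparison of changes with d = 0.5. The t-test needs 63.8, so 64 per arm, and has 80.1% power there. The repeated-measures interaction formula with two waves and f = 0.125 also gives N = 128. A second route is possible: four waves with f = 0.125 needs 90, and 90/0.7 = 128.6. Both routes reach 128 with independent women, so neither hides an allowance for groups. The power figures below belong to the first route.

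**Step 2: add the groups.** Design effect in the MBCP arm: DE = 1 + (6 − 1) × ICC.

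- True variance of the arm difference: (DE + 1)/64. Variance if groups are ignored: 2/64.
- SE ratio: sqrt((DE + 1)/2).
- Type I error if groups are ignored: 2 × (1 − Φ(1.96 / SE ratio)).
- True power: Φ(0.5 / sqrt((DE + 1)/64) − 1.96).

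Example at ICC 0.05: DE = 1.25, SE ratio = sqrt(1.125) = 1.061. Type I error = 2 × (1 − Φ(1.848)) = 6.5%. Power = Φ(0.5/0.1875 − 1.96) = Φ(0.707) = 76.0%.

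| ICC (assumed) | DE | SE ratio | Type I error if groups ignored | True power, 64 per arm |
|---|---|---|---|---|
| 0 | 1.00 | 1.000 | 5.0% | 80.7% |
| 0.01 | 1.05 | 1.012 | 5.3% | 79.8% |
| 0.05 | 1.25 | 1.061 | 6.5% | 76.0% |
| 0.10 | 1.50 | 1.118 | 8.0% | 71.6% |
| 0.20 | 2.00 | 1.225 | 11.0% | 63.7% |

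The table uses the normal approximation, hence 80.7% rather than 80.1% in the first row.

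**Step 3: check by simulation.** With 200,000 replicates, ten groups of six and one of four, and a t-test that ignores groups, rejection under the null was 4.9%, 6.4%, 7.8% and 11.0% at ICC 0, 0.05, 0.10 and 0.20.

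**Step 4: group size.** Six is an approximate size in the Design section and a minimum in the allocation section. Larger groups would make matters worse. As an illustration, groups of twelve at ICC 0.05 give DE = 1 + 11 × 0.05 = 1.55, type I error 8.3% and power 70.7%.

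**The case against.** **The model might contain the group.** A reader might infer that the 5% test is certainly not 5% and that women in one course are certainly treated as independent. The article does not support that for continuous outcomes. It says multi-level without naming the levels, and a list of predictors would not normally include a random effect. An analysis plan that is not shown could set one. This stands, so the statement about the analysis has to be conditional. It does not rescue the sample size, whose inputs are listed and whose result is reproduced without any ICC. Nor does it rescue a chi-square test, which has no place for a group level.

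**The ICC may be tiny.** This also stands. At ICC 0.01 the loss is about one point of power and 0.3 points of type I error.

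**Power was planned cautiously.** The Sample size section steps down from d = 0.81 and cites a mean effect of 0.59, and the Discussion admits that power is uncertain. At d = 0.59 the same formula gives about 88% power at ICC 0.05 and 85% at ICC 0.10. That softens the consequence. However, the Discussion attributes the uncertainty to the unknown effect of the comparison, not to grouping, and caution about the effect size does nothing for the type I error.

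**Adding 30% loss.** A reader might also combine the clustering with a 30% loss and arrive at a much lower power. The article does not support this. It describes the 30% as referrals to secondary care, and the Recruitment section continues until at least 64 women per arm have completed the programme. On the four-wave route the 30% may already be inside 128. Loss at the later follow-ups is still possible but is not quantified.

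**FoCC may cluster too.** FoCC is given by midwives, so women who share a consulting midwife may also be correlated. The number of midwives is not stated and this source is left out above.

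**Conclusion.** The point holds in two parts of different strength. First, without condition: the sample size carries no allowance for clustering in the MBCP arm, and any positive ICC lowers power below what the individual-level calculation gives. At d = 0.5 and groups of six it is about 76% at ICC 0.05 and 72% at ICC 0.10. Second, conditionally: the article does not name training group as a level. If it is omitted and the ICC is above zero, standard errors are understated by a factor of 1.06 at ICC 0.05 and 1.12 at ICC 0.10, and the test runs at about 6.5% and 8.0%. For dichotomous outcomes the methods named have no group level as described. All sizes rest on the assumed ICC, d = 0.5, equal total variance in the two arms and no clustering in FoCC. The matter is worth correcting but does not by itself invalidate the design.

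**What to change.** - **Sample size.** Restate the power of 64 per arm for groups of six over a declared ICC range, for example 0.01 to 0.10 (79.8% down to 71.6% at d = 0.5). No additional women are asked for.
- **Continuous outcomes.** Name a random training-group effect in the MBCP arm only. It must act on post-baseline change (group by time). An intercept that is constant over time cancels out of the change from T1 and leaves the standard error of time by condition uncorrected. Use small-sample degrees of freedom because there are only about 11 groups. Kenward-Roger needs REML, so choosing it means departing from the full-information maximum likelihood now named.
- **Dichotomous outcomes.** Replace the chi-square test and plain logistic regression with a group-aware method, such as a mixed logistic model or cluster-robust errors with a small-sample correction.

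The cost is a few lines of text, one model term and wider intervals: the standard error rises by about 6% at ICC 0.05 and 12% at ICC 0.10. Training-group membership must be kept in the dataset. The article does not say that it is, though class attendance is recorded. Treatment and assessments do not change.
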